### Prevention of result contamination

The standard test and the intervention test will be undertaken by different clinicians. The importance of only sharing the outcome with the parents and other staff once both evaluations have been documented will be stressed in site training. Inadvertent discussions between screeners will result in incident notification in the site file.

### Withdrawal of participants from the study

**
*Prior to registration.*
** This will include babies whose parents do not assent and those without an assigned NHS number. Additionally, if there are insufficient staff to undertake the study intervention or if the device is not working. In all cases, the reason for withdrawal following parent consent will be entered in the study database.

**
*Following registration.*
** Parents may withdraw their consent for data linkage or the use of the images in future development work by contacting the central research team. The reason for withdrawal reason, if given, will be documented on the eCRF in the trial database.

The data and images for registered babies in whom consent has been withdrawn will be retained in the study database and only event data up to the withdrawal date will be collected via data linkage. Given the absence of risk and the single use of the intervention, these numbers are not predicted to be high but further recruitment would be required to replace their loss.

**
*Usability and screening preference feedback from screeners.*
** Screeners undertaking either the standard red-reflex test or neocam imaging will attend site training prior to clinical use. Each will be asked to complete an anonymised usability questionnaire
^
12
^ during the study period.

**
*Definition of the end of the trial.*
** The end of trial will be 6 months after the last data capture via data linkage.

## Statistics and data analysis plan

### Statistical method

Given the rarity of cataract, and to maximise the data from eyes with cataract captured in the study, the abnormal eye will be selected as the index eye for data analysis where there is a unilateral abnormal screening result. Where the screening test is abnormal bilaterally, the right eye will be selected as the index eye.

A comparison of the relative sensitivity and specificity of the two tests will be possible using the counts of discordant pairs of screening tests, where one, and only one, of the neocam and standard test results within a baby are positive. Thus this relative comparison will be estimable in a short space of time for the recruited population using the expert image review as the gold standard. Hence much of the statistical inference can be performed before the long-term follow-up of the babies with both tests as negative.

For both the groups with and without congenital cataracts (as determined by the gold standard) the sensitivity and specificity, respectively, will be compared. McNemar’s test will provide a p-value, and a 2-sided 2.5% significance level used to account for the two contrasts. The absolute difference and odds ratios will also be estimated and provide with 95% confidence intervals. 

An estimate of the absolute values of, rather than differences between, sensitivity and specificity will be made following TSC expert review of the neocam images of babies with double negative screening tests in whom diagnostic and / or procedure codes indicating cataract were retrieved from HES on data linkage (since the cataract may have developed after birth). A detailed statistical analysis plan will be produced before the final database lock or before any interim analysis is performed.

Equivalent comparisons of sensitivity and specificity for each screening test will be made within ethnic groups and screener experience levels.

Quantitative comparison of the ease of the standard screening examination to the intervention will be analysed by screener questionnaire at the end of that staff member’s rotation on the maternity ward or at the end of the study recruitment period, whichever is sooner
^
12
^. Summary statistics reporting on the numerical or categorical questions will be provided.

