**Methods:**

140,000 newborn babies will be recruited into the study from at least 13 maternity units in England over an 18 month period. Babies will have both the standard red-reflex assessment and evaluation of the infrared-reflex using a prototype device. Since specialist gold-standard evaluation of every participant is impractical, bespoke data linkage requests to NHS England will be made. Data from the red-reflex evaluation and the presence of codes relating to cataract diagnosis and/or treatment in Hospital Episode Statistics (HES) will be retrieved for each participant a minimum of 6 months after their birth. This data will be used to calculate relative and absolute sensitivity and specificity for each screening test and comparison of accuracy using the McNemar test. Secondary outcome measures will include comparison of accuracy in different ethnic groups and screener usability scores.

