### Primary outcome measure

The primary outcome measures are:

 Screener evaluation “normal” or “abnormality suspected” of each eye using the standard test.Screener’s evaluation “normal” or “abnormality suspected” of each eye using the neocam digital imaging test.The gold standard evaluation (provided by data linkage +/- expert image review)

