**Figure 3. f3:**
[figure not shown]
Data linkage chart. Abbreviations: CI: Chief investigator, HES: Hospital Episode Statistics, ICD-10: HES diagnostic codes, OPCS: HES procedure codes, S4N: Smart4NIPE national database, TSC: Trial Steering Committee.

Specialist examination of 140,000 babies for the study to determine “true” disease (cataract) status would be impractical. Therefore, bespoke data linkage with Hospital Episode Statistics (HES) records at least six months after birth will be used to identify registered babies who have subsequently received a specialist diagnosis of cataract (based on both diagnostic and procedure codes). This, with additional expert review of the images when required, will provide the gold standard evaluation of disease status.

All babies referred for specialist examination (either due to abnormal standard, digital imaging or both) will undergo expert review of the digital images by the Chief Investigator (CI).Babies with double negative (evaluated as normal screening tests) but HES evidence of diagnostic/procedure codes indicating cataract will have their digital images reviewed by two independent expert ophthalmologists drawn from the Trial Steering Committee (TSC). This will determine if there was evidence of cataract at birth (which should have been detected by screening) to the gold standard or whether the cataract developed subsequently.10% of all double negative eye images will be routinely reviewed by the CI for quality control purposes. For cases where an abnormality is suspected on image review, a specialty referral will be organised for the baby within two weeks.

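### The article gives two reference standards for the relative comparison; if expert review of the neocam image decides, the sensitivity contrast is biased towards neocam

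*Protocol article*

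**What the plan says.** Four places in the protocol article bear on the reference standard.

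- **Statistical method.** The relative comparison is made "using the counts of discordant pairs of screening tests, where one, and only one, of the neocam and standard test results within a baby are" [abnormal], and is estimable quickly "for the recruited population using the expert image review as the gold standard". The section continues: "Hence much of the statistical inference can be performed before the long-term follow-up of the babies with both tests as negative". Its next paragraph applies McNemar's test to babies with and without cataract according to the gold standard, without saying again which one is meant.
- **Abstract, Methods.** On the linked red-reflex and HES data: "This data will be used to calculate relative and absolute sensitivity and specificity for each screening test".
- **Primary outcome measure.** "The gold standard evaluation (provided by data linkage +/- expert image review").
- **Acquisition of the gold-standard data (text under Figure 3).** HES diagnosis and procedure codes, at least six months after birth, identify cataract: "This, with additional expert review of the images when required, will provide the gold standard evaluation of disease status". Babies abnormal on either test are referred to a specialist, and the Chief Investigator reviews their digital images. For babies negative on both tests who have a HES cataract code, two independent experts use the images to decide if cataract was present at birth or "whether the cataract developed subsequently".

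**The concern.** The image under review is produced by the test being evaluated. Take a baby with cataract whose red reflex was called abnormal and whose neocam image was called normal. This baby is evidence against neocam. If the image does not show the opacity, an expert reading that image will also see no cataract. Should that reading settle disease status, the baby leaves the cataract group and neocam's miss disappears. Neocam-only positives are judged on the same image that made them positive, so nothing comparable removes evidence in neocam's favour. This is incorporation bias. It runs towards the study hypothesis and acts on a cell that is expected to hold very few babies.

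The abstract, outcome measures and gold-standard section would allow the HES diagnosis to keep such a baby in the cataract group. The Statistical method section names the image review. No rule says which wins when they disagree.

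**Working it through.** **Inputs from the article (Number of participants required).** Sensitivity 70% for red reflex and 95% for neocam; 35% discordant, the maximum these margins allow; McNemar's test, two-sided 2.5%; 90% power; 67 cataracts; 140,000 newborns. The abstract gives a prevalence of 1 in 3000.

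**Assumptions, not in the article.** f is the fraction of standard-only-positive cataracts that the neocam image does not show and that image review therefore removes. The split of discordant pairs under equal sensitivity is also assumed.

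**Step 1: cells among cataracts.** Neocam-only b and standard-only c satisfy b − c = 0.95 − 0.70 = 0.25 and b + c = 0.35. So b = 0.30, c = 0.05, both positive = 0.95 − 0.30 = 0.65, both negative = 0.

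**Step 2: reproduce the 67.** The exact McNemar test, enumerated over the binomial number of discordant pairs, first reaches 90% power at n = 67 (90.4%). The normal approximation gives 64.8, that is 65. The stated figure is reproduced.

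**Step 3: size of the vulnerable cell.** 67 × 0.05 = 3.35 standard-only cataracts expected.

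**Step 4: planning scenario with image review deciding.** Replace c by c′ = 0.05(1 − f). The cataract total becomes T = 0.65 + 0.30 + c′.

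| f | T | Neocam 0.95/T | Standard (0.65 + c′)/T | Difference |
|---|---|---|---|---|
| 0 | 1.000 | 95.0% | 70.0% | 25.0 points |
| 0.5 | 0.975 | 97.4% | 69.2% | 28.2 points |
| 1 | 0.950 | 100% | 68.4% | 31.6 points |

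At f = 1 neocam's sensitivity is 100% by construction, since the design assumes no double-negative cataracts.

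**Step 5: truly equal sensitivity.** Set b = c, then thin the standard-only cell to c′ = c(1 − f). With N true cataracts, the discordant count is m ~ Bin(N, b + c′). Given m, the neocam-only count is Bin(m, b/(b + c′)). The table gives the probability that the exact McNemar test at two-sided 2.5% rejects in neocam's favour (nominal 1.25% per side). N is 67 (the target) or 47 (140,000/3000 = 46.7).

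| f | 15%+15%, N=47 | 15%+15%, N=67 | 5%+5%, N=47 | 5%+5%, N=67 |
|---|---|---|---|---|
| 0 | 0.7% | 0.7% | 0.1% | 0.3% |
| 0.1 | 1.1% | 1.2% | 0.1% | 0.4% |
| 0.25 | 2.3% | 3.0% | 0.2% | 0.6% |
| 0.5 | 7% | 12% | 0.3% | 1.2% |
| 1 | 57% | 89% | 0.8% | 5.0% |

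The exact test is conservative. In the last cell the uncorrected chi-square version of McNemar's test gives 11.8%.

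**Step 6: specificity.** Removed cataracts become false positives of the standard test. Even if all are removed, that is 67 × 0.05 = 3.35 babies in the planning scenario and 67 × 0.15 = 10 babies with 15%+15%. Over 140,000 these are 0.002 and 0.007 percentage points.

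**Step 7: double negatives.** A baby negative on both tests is in neither discordant cell. Reclassifying it from the image changes the absolute sensitivity of both tests and leaves McNemar's counts as they were.

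**The case against.** The strongest reply is that the Statistical method section describes only what can be estimated early. It does not say that image review stands alone in the final analysis. The McNemar paragraph refers back to the gold standard, which other sections base on linkage, and the article nowhere says that a clean image overrides a specialist diagnosis. This stands: that such a baby would be called cataract-free in the final primary analysis is an inference. What remains is that one section names a reference the others do not, says much of the inference can rest on it, and leaves disagreements unresolved.

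A second reply is that the screener's reading is the index test and an expert's reading is the reference. Cataracts that are visible but misread by the screener are recovered and still count against neocam. This also stands, and it is why f may be small. At f = 0 there is no bias, and at f = 0.1 the error rate stays within the nominal 1.25%. Only opacities that the image fails to show are lost. The article itself foresees blur, eye closure and scans of insufficient quality, but gives no rate.

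Three stronger readings are tempting and are not supported:

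- That both primary contrasts are biased materially. The shift in specificity is at most about 10 babies in 140,000.
- That reclassifying HES-coded double negatives favours neocam in the comparison. It raises both absolute sensitivities and does not touch the discordant counts. The article's reason for doing it, that some cataracts arise after birth, is sound.
- That the device's inventor determines the reference. The article says the study lead invented the device and that the Chief Investigator reviews the images. That these are one person is an inference, and the point does not depend on it.

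**Conclusion.** The point holds as an unresolved contradiction with a one-sided risk. As worded, the Statistical method section lets the index test's own image decide disease status for the discordant babies, while the abstract, the outcome measures and the gold-standard section rest on HES diagnosis. If the image decides, the bias in the sensitivity contrast can only favour neocam.

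Its size cannot be fixed from the article, because f and the discordance under equal sensitivity are both assumptions. The range runs from no practical inflation (f up to about 0.1, or low discordance with the exact test) to severe (57% with 47 cataracts and 89% with 67, at 15%+15% and f = 1). The severe end requires that every standard-only cataract is invisible on the image, with no screener misreadings at all, so it is a bound and not a forecast. It still merits correction before analysis: only about 3.4 babies are expected in the affected cell, and the specialist diagnosis is already due to be linked.

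**What to change.** Reconcile the abstract, Primary outcome measure, Acquisition of the gold-standard data and Statistical method sections, and carry the same wording into the analysis plan:

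1. For screen-positive babies in the primary McNemar comparison, disease status comes from the specialist diagnosis obtained through HES linkage, made without the neocam image. It prevails over image review when the two disagree.
2. Image review as reference is a labelled sensitivity analysis, reported with the number of standard-only-positive babies whose status differs between the two references.
3. Remove the statement that expert image review is the gold standard for the relative comparison.

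Separately, and with no effect on McNemar's test, report absolute sensitivity both with and without the image-based reclassification of double negatives who have a HES cataract code. Counting all of them as missed would include cataracts that arose after birth, so neither estimate is plainly the right one alone.

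The cost is wording, plus a delay: the primary p-value waits for the first HES extract. McNemar's test still does not need the follow-up of double negatives, so the article's argument for early inference survives in that respect.

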### Secondary objectives

Comparison of accuracy between tests with respect to ethnicity, comparison of accuracy between tests with respect to screener experience and usability feedback and test preference.

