### Registration

Once the eICF is documented in the maternal database record, verbal assent is sought prior to digital imaging. The process of the baby’s registration into the study occurs when the clinician inputs the site and user code, maternal NHS number, baby’s NHS number and date of birth (DOB) into the neocam digital imaging device. A software algorithm checks validity of the maternal and baby NHS number to mitigate against data entry error.

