### Acquisition of the intervention data

Images from the neocam device are uploaded daily by connecting the device with a Trust computer via a USB cable. The images are copied to the secure study database linked by the maternal NHS number to create the electronic case report form (eCRF). More than one eCRF can be registered under the same maternal record (for instance for multiple births). The images are then deleted from the device itself. In addition to the images, the information uploaded to study database includes: site and user-role code, maternal NHS number, baby’s NHS number, baby’s DOB, date of imaging and the infrared-reflex evaluation for each eye.

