### Acquisition of the standard screening data

Red-reflex screening results are routinely inputted into the nationwide Smart4NIPE (S4N) web-based database controlled by NHSE. This data includes the baby’s NHS number, DOB sex, ethnicity, screener role and red-reflex evaluation codes. This data will be retrieved through bespoke data linkage with NHSE records. Any babies with “abnormality suspected” evaluations on their standard screening tests will have this documented in the study database after both screening tests have been completed.

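### Within-stratum paired tests do not fit screener experience, where a pair has two screeners and the listed data hold role, and do not test whether the difference between tests varies by ethnicity

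*Protocol article*

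**What the plan says.** The Secondary objectives are: "Comparison of accuracy between tests with respect to ethnicity, comparison of accuracy between tests with respect to screener experience and usability feedback and test preference". Statistical method turns the first two into an analysis: "Equivalent comparisons of sensitivity and specificity for each screening test will be made within ethnic groups and screener experience levels". The comparison to be repeated is the paired one described just before it: McNemar's test at a two-sided 2.5% level, with absolute differences, odds ratios and 95% confidence intervals.

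On who does the tests, Prevention of result contamination says: "The standard test and the intervention test will be undertaken by different clinicians".

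On what is known about the screener:

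- For the infrared test, Acquisition of the intervention data lists "site and user-role code, maternal NHS number, baby’s NHS number, baby’s DOB, date of imaging and the infrared-reflex evaluation for each eye". Registration words the first item differently: "the clinician inputs the site and user code, maternal NHS number, baby’s NHS number and date of birth (DOB) into the neocam digital imaging device".
- For the red-reflex test, Acquisition of the standard screening data says: "This data includes the baby’s NHS number, DOB sex, ethnicity, screener role and red-reflex evaluation codes".
- The usability questionnaire is anonymised (Usability and screening preference feedback from screeners).

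Number of participants required sizes the study for the overall sensitivity comparison and claims no power for subgroups.

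**The concern.** There are two separate problems.

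**Experience.** A McNemar pair is one baby with two results. The results come from two people, who may differ in experience. A stratum of pairs at one experience level is therefore not defined until the plan says whose level counts. Using one screener's level leaves the other's uncontrolled, and keeping only pairs with matching levels discards data. The listed fields also do not hold experience for either screener.

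**Ethnicity.** Background and rationale and Review of existing evidence argue that darker pigmentation hampers the red-reflex test and that the infrared image avoids this. That is a claim that the difference between the tests changes with ethnicity. A set of within-group p-values does not test it. A larger group can give a small p-value and a smaller group a large one when the true difference is the same in both.

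At stake are one secondary objective that is not executable as worded and another addressed by the wrong contrast. The experience part is also a matter of timing: a later analysis plan can change a model, but it cannot create a variable that was not collected.

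**Working it through.** **1. The experience stratum.** Set the fields side by side.

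| | Infrared test | Red-reflex test |
|---|---|---|
| Screener | one clinician | a different clinician |
| Screener field listed | "site and user-role code" (a user code in Registration) | role, within "ethnicity, screener role and red-reflex evaluation codes" |
| Experience field listed | none | none |
| Questionnaire | anonymised, not linkable to a result as described | same |

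If the user code in Registration identifies an individual, experience might be looked up for the infrared screener. It would still be missing for the red-reflex screener.

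**2. Reproducing the sample size.** Inputs from Number of participants required: sensitivities 70% and 95%, discordance 35%, two-sided 2.5%, 90% power.

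- p10 + p01 = 0.35 and p10 − p01 = 0.25, so p10 = 0.30 (infrared only) and p01 = 0.05 (red-reflex only).
- Exact power = Σ over m of P(M = m) × P(reject | m), with M ~ Binomial(n, 0.35) and, given m, infrared-only pairs ~ Binomial(m, 0.30/0.35).
- n = 66 gives 0.898 and n = 67 gives 0.904. The protocol's 67 is reproduced.

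**3. Sensitivity within an ethnic group.** With m discordant pairs all in one direction, the exact two-sided p is 2 × 0.5^m: 0.031 for m = 6 and 0.016 for m = 7. At 2.5% at least 7 are needed. At 35% discordance that corresponds to 7/0.35 = 20 cataracts in the group.

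The protocol plans on 67 cataracts. The Abstract's prevalence of 1 in 3000 gives 140,000/3000 = 46.7. Group shares are not stated, so they are assumed over a range. Exact power at 2.5% for the full 25-point effect:

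| Share of cataracts | Cases of 67 | Power | Cases of 46.7 | Power |
|---|---|---|---|---|
| 10% | 7 | 0.00 | 5 | 0.00 |
| 20% | 13 | 0.04 | 9 | 0.00 |
| 30% | 20 | 0.21 | 14 | 0.06 |
| 50% | 34 | 0.55 | 23 | 0.29 |
| 70% | 47 | 0.74 | 33 | 0.53 |

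If the 2.5% level were not carried into subgroups, the exact test at 5% with 67 cataracts would give 0.00, 0.11 and 0.32 at shares of 10%, 20% and 30%.

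**4. Contrast between groups, sensitivity.** The variance of the paired difference per case is 0.35 − 0.25² = 0.2875. For two groups, SE = √(0.2875/n1 + 0.2875/n2), and the difference detectable with 80% power at 5% is (1.96 + 0.84) × SE. With 67 cases:

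- 50:50 split: SE 0.131, detectable difference 37 points.
- 20:80 split: SE 0.164, detectable difference 46 points.

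Both exceed the 25-point overall effect, so an interaction on sensitivity would also be imprecise.

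**5. Specificity by ethnicity.** Background and rationale puts red-reflex referrals at 10 times the frequency expected from prevalence. Removing true positives at 70% sensitivity, the false-positive rate is about (10 − 0.7)/3000 = 0.0031. Suppose the infrared test halves that rate, with maximum discordance (assumptions). Approximate McNemar power at 2.5% is then:

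| Share of babies | Babies | Red-reflex false positives | Power |
|---|---|---|---|
| 5% | 7,000 | 22 | 0.37 |
| 10% | 14,000 | 43 | 0.67 |
| 20% | 28,000 | 87 | 0.94 |

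**The case against.** The best defence is that this is a secondary analysis for which no power is claimed, so small counts make it imprecise rather than wrong. The planned comparison includes differences and odds ratios with intervals, and nothing says that conclusions will rest on which groups reach significance. The stated objective, a comparison between tests with respect to ethnicity, can be read as a comparison within each group. The interaction is inferred from the background sections. A detailed analysis plan is promised, and experience bands and model form are commonly left to it.

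Much of this stands. Low subgroup power is not in itself an error, and the model can be settled in the analysis plan. What remains is that within-group tests do not address the pigmentation rationale, and that no analysis plan can supply a screener variable missing from the data.

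Several stronger readings are tempting, but the documents do not support them:

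- *The secondary objectives cannot be answered.* Specificity by ethnicity can be compared in all but small groups, and usability and preference are untouched.
- *The experience analysis is impossible.* Each test could be tabulated by its own screener's level, and pairs with matching levels form a valid stratum. The text is ambiguous about which is meant.
- *Experience can never be recovered.* The user code in Registration leaves the infrared screener's identity open.
- *A group with about 9 cataracts can never reach significance.* At the expected 3 discordant pairs the smallest p is 2 × 0.5³ = 0.25, but more discordant pairs could occur. The chance of 7 or more among 9 is about 1%: remote, not zero.

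**Conclusion.** The point holds in this limited form and is worth correcting; the primary analysis is not affected. Screener experience is not a defined stratum for pairs made by two clinicians, and the listed fields hold role. For ethnicity, repeated McNemar tests are the wrong contrast for the stated rationale. For sensitivity they are close to uninformative in any group with 30% or less of the cataracts: power is at most about 0.21 with 67 cataracts and 0.06 with 47.

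These figures rest on the protocol's 25-point effect and 35% discordance, on assumed group shares, on the exact test, and on carrying the 2.5% level into subgroups. The low power in small groups does not depend on choosing 47 rather than 67. The specificity figures rest on the referral ratio and on an assumed halving of false positives.

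**What to change.** **Experience.** Reconcile the user code in Registration with the user-role code in Acquisition of the intervention data. Then take one of two routes:

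- Restate the objective and analysis as screener role. Use a model with two rows per baby, one per test, clustered on baby, with role entered as a covariate specific to each test.
- If experience is wanted, record it before site training for the screeners of both tests, in a form that links to each result. A band attached only to the infrared user code is not enough, because role is the only screener field listed from the national database for the red-reflex test. Study status places the study before site training, so the change can still be made. Data handling and record keeping says that saved records cannot be edited.

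**Ethnicity.** Add a test-by-ethnicity interaction with confidence intervals, resting mainly on specificity. Report sensitivity by group as counts with exact intervals and no p-values, since an interaction on sensitivity is sparse too.

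**Cost.** Renaming to role and changing the model need only wording in the protocol and analysis plan, and no extra babies. Recording experience for both sets of screeners needs an added data item and a link to each red-reflex result. The downside is the loss of subgroup p-values for sensitivity.
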